### Study outcomes and follow-up schedule

#### Rationale for outcome chosen

Myopia is an eye disorder in which light focuses in front of the retina, but not right on the retina, and mostly because of the excessive axial elongation of the eyeball. In the clinic, two valid and reproducible indicators—subjective refraction (SER in diopters) and AL (mm) under cycloplegia—are considered to be more relevant for evaluating changes in subjects with myopia. In addition, several influencing factors are related to the evaluation of myopia. Thus, in the present study, primary, secondary, and exploratory outcomes will be evaluated during the follow-up period according to the schedule (Fig. 1 and Table 1).

**Fig. 1 Fig1:**
[figure not shown]
Schematic of the trial design

**Table 1 Tab1:** Schedule of assessments and examination items

Procedures/measurements		Enrollment (− 2 to 0 week)	Baseline	1 Week (± 1 day)	1 Month (± 3 days)	3 Months (± 7 days)	6 Months (± 14 days)	12 Months (± 21 days)	18 Months (± 28 days)	24 Months (± 35 days)	30 Months (± 42 days)	36 Months (± 60 days)
Consent form signed			x									
Basic information	Demographics	x										
	History	x	x	x	x	x	x	x	x	x	x	x
Refraction	Noncycloplegic autorefraction	x	x				x	x	x	x	x	x
	Subjective refraction	x	x				x	x	x	x	x	x
	Cycloplegic subjective refraction^a^		x				x	x	x	x	x	x
	Cycloplegic autorefraction^a^		x				x	x	x	x	x	x
	Peripheral refraction^a^		x				x	x	x	x	x	x
Visual acuity	Habitual spectacle visual acuity	x	x				x	x	x	x	x	x
	Best corrected visual acuity	x	x				x	x	x	x	x	x
Ocular alignment	Cover test (distance, near)	x										
	Phoria (distance, near)		x				x	x	x	x	x	x
Accommodation	Lag		x				x	x	x	x	x	x
	Amplitude		x				x	x	x	x	x	x
Eye examinations	Slit-lamp examination, external ocular health check	x	x				x	x	x	x	x	x
	IOP measurement	x	x				x	x	x	x	x	x
	Pupil size		x				x	x	x	x	x	x
	Keratometry		x				x	x	x	x	x	x
	Contrast sensitivity											
	Stereopsis		x				x	x	x	x	x	x
	Axial length (mm)^a^ (IOLMaster [Zeiss, Oberkochen, Germany], measure between 9:00 and 11:00 a.m.)		x				x	x	x	x	x	x
	Choroidal thickness measurement		x				x	x	x	x	x	x
	Fundus examination^a^		x				x	x	x	x	x	x
Questionnaire	Visual habits		x									x
	Spectacle lens performance		x									x

*IOP* intraocular pressure

^a^With cycloplegia

#### Primary outcome

The primary outcome is to determine whether DIMS lenses are noninferior to PALs for the prevention of myopia progression by evaluating the cycloplegic SER changes in two groups of subjects. For the primary outcome analyses, myopia progression over 3 years will be determined by the difference in the subjective SER between baseline and the last follow-up visit. Other measurements obtained at follow-up visits are considered secondary outcome measures.

Procedures for subjective refraction will be as follows [10]:
Starting with autorefraction and refine subjectivelyOcclude the left eyeDetermine best sphere firstDetermine cylindrical errorRefine sphere using + 1.00 diopter blur back test monocularly and finish by offering a binocular + 0.25 diopters additionalBinocular balance (prism dissociation); stop when no difference between the upper and lower line

#### Secondary outcome

The secondary outcome is to determine whether DIMS lenses are noninferior to PALs for the prevention of axial elongation (mm) determined by noncontact interferometry measurements [10] in the two groups of subjects at baseline and the last follow-up visit.

#### Exploratory outcomes

Several innate and environmental factors are useful in understanding the control of myopia progression [6, 8, 15], including age and refractive error at onset, family history (e.g., parental myopic status), visual and environmental habits (e.g., near work time, outdoor time, spectacle wear time, brightness of light exposure), binocular vision (e.g., accommodative lag, elevated accommodative convergence to accommodation ratio), peripheral refraction, pupil size, and treatment compliance. Thus, we plan to evaluate these factors as secondary and exploratory outcome measure items in the present study, as shown in Tables 1, 2, 3, and 4.

**Table 2 Tab2:** Wearing experience questionnaire - 1

Activities		Content		
Parental myopia		0 person	1 person	2 persons
Clarity	Short distance	Good	Fair	Poor
	Intermediate vision distance	Good	Fair	Poor
	Long distance	Good	Fair	Poor
Time wearing spectacles (h/d)	Weekdays (Monday to Friday)			
	Weekends (Saturday to Sunday)			
Time spent at work	Near work (h)			
	Middle-distance work (h)			
Time spent on activities	Outdoor			
	Indoor			
Sleeping time				

Modified from Reference [10]

**Table 3 Tab3:** Wearing experience questionnaire - 2

		Poorest	➞	Acceptable	➞	Fair	➞	➞	Good	➞	Excellent
1	Vision at a distance (clarity)	1	2	3	4	5	6	7	8	9	10
2	Vision stability at a distance	1	2	3	4	5	6	7	8	9	10
3	Clarity of vision for intermediate distances (e.g., computer, watching television)	1	2	3	4	5	6	7	8	9	10
4	Clarity of vision for near tasks (e.g., reading, using smartphone)	1	2	3	4	5	6	7	8	9	10
5	Vision stability at close range	1	2	3	4	5	6	7	8	9	10
6	Vision stability at a distance	1	2	3	4	5	6	7	8	9	10
7	Vision comfort	1	2	3	4	5	6	7	8	9	10
8	Vision outdoors	1	2	3	4	5	6	7	8	9	10
9	Ease of lens adaption	1	2	3	4	5	6	7	8	9	10
10	Overall performance	1	2	3	4	5	6	7	8	9	10

Modified from Reference [10]

**Table 4 Tab4:** Wearing experience questionnaire - 3

		Do you have the following symptoms when you wear spectacles?									
		Never	➞	Seldom	➞	Sometimes	➞	➞	Often	➞	Always
1	Blurred vision at a long distance	1	2	3	4	5	6	7	8	9	10
2	Blurred vision at an intermediate distance (e.g., computer)	1	2	3	4	5	6	7	8	9	10
3	Blurred vision at a short distance (e.g., reading, smartphone)	1	2	3	4	5	6	7	8	9	10
4	Ghosting image	1	2	3	4	5	6	7	8	9	10
5	Unstable vision at a distance	1	2	3	4	5	6	7	8	9	10
6	Unstable vision at close range	1	2	3	4	5	6	7	8	9	10
7	Difficulty or slowness in refocusing your eye from one distance to other	1	2	3	4	5	6	7	8	9	10
8	Eyestrain	1	2	3	4	5	6	7	8	9	10
9	Double vision	1	2	3	4	5	6	7	8	9	10
10	Dizziness	1	2	3	4	5	6	7	8	9	10
11	Headache	1	2	3	4	5	6	7	8	9	10

Modified from Reference [10]

#### Cycloplegia protocol

All of the refraction and AL measurements will be obtained by a standard cycloplegia protocol. The recommended dosage for cycloplegic refraction is two drops of 1% tropicamide given 5 min separately. Cycloplegic refraction outcome measures will be obtained 30–45 min after the first drop of tropicamide is instilled, which ensures the maximal cycloplegic effect. Refraction will be measured with an open-field autorefractor (Shin-Nippon NVision-K 5001 autorefractor; Rexxam Co., Osaka, Japan). The AL will be measured by using an IOLMaster system (Carl Zeiss, Oberkochen, Germany). For SER and AL, five measurements will be obtained at each visit and then averaged for each eye for statistical analysis.

#### Follow-up examination and measurement schedule

All of the ophthalmic exanimation measures will be assessed at baseline, 1 month, 3 months, 6 months, and then every 6 months until 3 years after randomization. The differences in all of the mean values at each follow-up visit from baseline will be analyzed. Additionally, to avoid binocular interaction bias, only one eye will be randomly chosen for analysis of the study outcomes.

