#### Apollo PALs

The Apollo PALs comprise an asymmetrical MD design with a 3 MD zone, including a + 2.50 diopters full positive power superior zone, an 80% full MD power nasal zone, and a 60% full MD power temporal zone.

Both of the spectacle lenses are designed to simultaneously provide clear distance vision for the wearer and introduce MD for the peripheral retina by providing a plane in front of the retina, resulting in signals being received as blurred images on the retina [5]. All of the children will be instructed to wear lenses all the time throughout the whole study. The use of atropine eye drops of any concentration will not be permitted for any participant during the study.

The final distance prescription of the spectacles will be determined on the basis of cycloplegic subjective refraction by the masked optometrist. The spectacle lenses will be replaced and upgraded when the change in SER is 0.5 diopters or more in either eye compared with refraction while wearing spectacles.

At the initial spectacle dispensing and at each follow-up visit, subjects and their guardians will receive face-to-face instruction about the purpose, use, and care of the lenses. In addition, investigators will explain the etiology and pathology of myopia, emphasize the importance of adherence to the follow-up protocol for evaluating myopia progression, and provide notifications regarding the follow-up ophthalmic examinations. In addition, the SMO from PKUPH will provide phone call reminders before each visit to enhance compliance with the present clinical trial.

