### Randomization and masking

The research coordinator will guide the participants to perform and finish all of the examinations, go through the results, and mask the groups to which the subjects belong. In addition, the coordinator will contact individuals before their follow-up visits.

The unmasked investigator (UMI) will be responsible for group allocation (i.e., allocating all of the children into either the DIMS lens group or PALs group through the sequence generation method [a random number table] at a 1:1 allocation ratio). In addition, the UMI will also be in charge of spectacle lens fitting, aftercare, performance assessments, data recording, and answering questions from participants and their parents/gradients.

The MI will be responsible for ophthalmic assessment and data measurements, blinded to the allocation, and not allowed to handle spectacle lenses throughout the study.

In addition, to avoid accidental unmasking, the spectacles will be kept by the UMI until the subjects finish the examination by the MI. Additionally, to avoid selection bias, allocation concealment will be ensured until the participants and their parents/guardians have been recruited into the clinical trial after the individuals finish all of the baseline examinations. During the clinical trials, neither the participants (together with their parents/guardians) nor the MI will be aware of group allocation.

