### Data management and data analyses

Data from the two groups will be presented as the mean ± SD, except for the gender and patient number in each group, which will be presented as proportions. Data from a random eye will be used for data analysis according to a random table, considering the high correlation between the two eyes of the same participant. Baseline group data will be analyzed by using unpaired *t* tests. Repeated measures analysis of variance will be used to determine changes from baseline over time and between the two study groups. Bonferroni corrections will be used for post hoc comparisons. Correlations between changes will be calculated using Pearson’s correlation coefficient.

In the present study, all randomized participants will be included in the data analysis, regardless of protocol adherence. Missing data will not be included in the following analysis and will not be imputed from the time point of dropout. An interim analysis of the primary endpoint will be performed by an independent statistician when 50% of the participants have been allocated and have completed a 6-moth follow-up examination.

Once the subjects are enrolled, retention efforts will be addressed with participants and parents/guardians. Coordinators, study investigators, and examination staff will (1) provide periodic communication about the clinical trial and myopia control strategies for the subjects, (2) provide feedback regarding the eye care data of the subjects, and (3) provide reminders of the follow-up visit and final visit.

An internal data monitoring committee (DMC) will be established and will consist of ophthalmologists who are not involved in running the trial, statistical experts, and members of the ethics committee. The DMC chair will be [name], the PKUPH ethics committee director. Data monitoring will be performed quarterly by the DMC, including monitoring for data completeness, safety information, adverse events, and so forth. No auditing will be performed through a professional organization. The integrity of the trial for each subject will be cross-checked between sites to ensure the appropriate allocation and completeness, accuracy, timeliness of data collection, and so forth.

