In the present study, the main adverse event will likely be decreased visual clarity and discomfort after wearing glasses. Adverse events occurring after the dispensing of spectacle lenses will be recorded, and investigators will address the signs and symptoms of the subjects in a timely manner.

Participants may withdraw from the study for any reason at any time. In addition, the investigators may also withdraw participants from the study to protect their safety. All study-related information will be stored securely in locked file cabinets in the research laboratory at each study site. All of the records containing personal identifiers, such as names and informed consent, will be stored separately from data records identified by code number.

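### Habitual-spectacle acuity is taken in pre-trial eyewear at baseline and in the study lenses from month 6, so its change from baseline mixes the prescription update with the lens effect

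*Protocol article*

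**What the plan says.** Table 1 of the protocol article lists "Habitual spectacle visual acuity" at enrollment, at baseline and at months 6, 12, 18, 24, 30 and 36. Best-corrected acuity is marked at the same visits.

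The section on the follow-up examination and measurement schedule states a general rule: "The differences in all of the mean values at each follow-up visit from baseline will be analyzed". The data analysis section gives the model: "Repeated measures analysis of variance will be used to determine changes from baseline over time and between the two study groups". Neither place exempts any measure.

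Three other statements settle which eyewear is on the child's face:

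- Under Randomization and masking, allocation stays concealed until participants have been "recruited into the clinical trial after the individuals finish all of the baseline examinations".
- Under Apollo PALs, in text that covers both lenses: "The final distance prescription of the spectacles will be determined on the basis of cycloplegic subjective refraction by the masked optometrist".
- In the same place, for the treatment period: "All of the children will be instructed to wear lenses all the time throughout the whole study". Lenses are then renewed as refraction changes: "The spectacle lenses will be replaced and upgraded when the change in SER is 0.5 diopters or more in either eye".

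On safety, the data management section expects that "the main adverse event will likely be decreased visual clarity and discomfort after wearing glasses".

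**The concern.** A change from baseline is interpretable when the same thing is measured at both ends. Here the row keeps its name while the object measured changes. Before dispensing, the habitual correction is the child's own. It cannot be a progressive or bifocal lens, because earlier use of those is an exclusion, and no eligibility criterion requires it to be up to date or even to exist. After dispensing it is the study lens, made to a fresh cycloplegic refraction.

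A fresh prescription by itself tends to improve acuity, while a defocus design may reduce it. The within-arm change adds the two together. This matters because the trial has no single-vision arm, so a loss of clarity common to both lenses cannot appear in the comparison between arms. The within-arm figure is where a reader would look for it, and decreased clarity is the adverse effect that the article itself anticipates.

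**Working it through.** The article states no figure for habitual acuity, so there is none to reproduce. The check has three parts.

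**1. Order of procedures.** Baseline examinations come first, then allocation, then a lens made to the cycloplegic refraction, then full-time wear. The term habitual is not defined, but this order rules out the study lens at baseline and makes it the habitual spectacle afterwards.

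**2. Within-arm change.** Work in logMAR, where positive means worse. Let u be the baseline deficit of habitual against best-corrected acuity, L the loss caused by the study lens, and p the loss from progression not yet corrected since the last lens update. If best-corrected acuity is stable:

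- baseline value = best-corrected + u
- follow-up value = best-corrected + L + p
- change = L + p − u

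Just after an update p is about 0, and the change is L − u. The article gives neither L nor u. Over an assumed range:

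| Assumed u | Change if L = 0.05 | Change if L = 0.10 |
|---|---|---|
| 0 | +0.05 | +0.10 |
| 0.05 | 0.00 | +0.05 |
| 0.10 | −0.05 | 0.00 |
| 0.20 | −0.15 | −0.10 |
| 0.30 | −0.25 | −0.20 |

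The sign is wrong whenever u exceeds L. At u = 0 there is no distortion.

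**3. Between-arm contrast.** Randomization gives both arms the same expected u, so it cancels. A simulation with 300 per arm confirmed this. It assumed mean u = 0.20 (SD 0.15), L = 0.10 for DIMS and 0.05 for PALs, and follow-up SD 0.08. The mean within-arm changes were −0.10 and −0.15, both apparent gains. The difference between arms was 0.050, equal to the true 0.05.

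Precision does suffer. With baseline SD sb, follow-up SD sf and correlation r, Var(change) = sb² + sf² − 2·r·sb·sf, to be compared with sf². All SDs and correlations here are assumed.

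- Least extreme case (sb 0.15, sf 0.10, r 0.3): (0.0225 + 0.0100 − 0.0090)/0.0100 = 2.35.
- Middle case (sb 0.25, sf 0.08, r 0.1): (0.0625 + 0.0064 − 0.0040)/0.0064 = 10.1, so the change has SD 0.255 against 0.08.
- Most extreme case (sb 0.35, sf 0.06, r 0.1): (0.1225 + 0.0036 − 0.0042)/0.0036 = 33.9.

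The article expects about 40% loss to follow-up, which leaves 300 × 0.6 = 180 per arm. The 95% half-width is 1.96 × SD × √(2/180). In the middle case that is 0.053 logMAR for the change and 0.017 for the follow-up value alone.

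**The case against.** The strongest reply is that little rests on this row. Habitual acuity is not named as a primary or secondary outcome and is not among the examples of exploratory ones. It enters only through the Exploratory outcomes section's general reference to Table 1. The rule on differences from baseline is one loosely worded sentence in a condensed article, and the sentence before it puts all ophthalmic measures at months 1 and 3, which Table 1 does not. The trial's own question is DIMS against PALs, and that contrast is unbiased. All of this stands, and it limits the weight of the point. It does not remove the point, because the rule is stated for all measures and is wrong for this one. That is different from detail left to an analysis plan.

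A reader might go further in three ways that the article does not support:

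- **That the loss of clarity would be hidden from the trial.** Adverse events after dispensing are recorded, and the questionnaires ask about clarity and blur in the worn spectacles, with a repeat at month 36.
- **That the change measures only the prescription update.** It measures the update and the lens effect together.
- **That children without glasses at entry drop out of the analysis.** The article says missing data are neither included nor imputed from the time of dropout. It does not say how acuity is recorded for a child who has no spectacles, so exclusion would be an inference.

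It is also fair to object that comparison with same-visit best-corrected acuity is not clean. It equals L + p and so keeps a prescription artefact of its own, up to about the 0.5 D update threshold. The fix has to say so.

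**Conclusion.** The point holds as a minor one. For habitual spectacle acuity, the stated change from baseline compares two kinds of eyewear, and within an arm it can show a gain despite a real loss. That happens only if the baseline deficit exceeds the lens-induced loss, and the article gives neither value. The gain of 0.05 to 0.25 logMAR for L = 0.05 and u = 0.10 to 0.30 is therefore an illustration, not a prediction. So are the variance ratios of about 2.3 to 34.

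It may be tempting to conclude that the comparison of DIMS with PALs on this measure is biased. It is not: allocation follows the baseline measurement, so the old eyewear adds noise and no systematic difference. Refraction and axial length, the primary and secondary outcomes, are not affected.

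**What to change.** Add two or three sentences to the analysis section:

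- Exempt habitual spectacle acuity from the change-from-baseline rule, and use the pre-trial value only to describe the population.
- At each visit from month 6, compare the arms directly on acuity in the study spectacles. Adjustment for baseline best-corrected acuity is optional and may gain little, because entry requires 20/20 or better and the covariate has a narrow range.
- For any within-arm statement, report study-spectacle acuity minus best-corrected acuity at the same visit. Describe it as lens effect plus uncorrected progression since the last lens update, not as lens effect alone.

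Two inconsistencies bear on this text and should be reconciled with it. Table 1 and the follow-up section disagree on whether acuity is taken at months 1 and 3. The lens-update criterion is given as a change greater than 0.50 D under Study design and recruitment, but as 0.5 D or more under Apollo PALs.

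No new test or visit is needed, since both acuities are already scheduled together from month 6. The cost is the wording, and a within-arm figure that still needs the stated caveat.

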#### Training of the study staff

All staff from each site will be trained under the control of PKUPH, including in taking the standard measurements related to the primary, secondary, and exploratory outcomes; implementing the clinical trial protocol; managing data; and addressing key issues raised by participants. The training process is necessary for consistency, reproducibility, and repeatability. The standard training program will include but not be limited to obtaining BCVA, refraction, AL, binocular vision, corneal curvature, and peripheral refraction measurements; administering the questionnaire; and recording data. During the whole study, the SMO from PKUPH will play an internal quality control role to ensure the study is performed in a uniform manner at all study centers.

### Sample size calculation

Estimation of the sample size is based on the two following methods: statistical analysis and recommendations from review articles.

#### Statistical analysis

The two-sample *t* test for noninferiority statistical analysis was used for the sample size calculation. The noninferiority null hypothesis is that the refractive error, measured by SER, will be worse with DIMS lenses than with PALs for the treatment of myopia, and the rejection of this null hypothesis is powered to detect a noninferiority margin (Δ) of < 10% [15]. According to previously published articles, the 2-year difference in myopia progression with DIMS is 0.44 ± 0.09, whereas the difference in myopia progression with PALs is 0.20 ± 0.08 [10, 15, 16]. Thus, the mean difference between DIMS lenses and PALs is 0.22. Because the detected variation in myopia is ~ 0.25–0.5, we chose 0.5 as the SD factor. Other parameters used include a significance level of 0.05, 95% confidence interval (two-sided), 80% power, and 1:1 allocation. Based on these parameters, the estimated sample size for each group is 201 subjects. On the basis of our previous experience with clinical trials for treating myopia and other published data, we estimated the rate of subject loss to follow-up over 3 years to be ~ 40%. Considering these factors together, the estimated sample size for each group is 282.

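### The 201 per group and its 80% power do not follow from the stated inputs under the declared noninferiority test, and the printed difference of 0.22 does not match 0.44 and 0.20

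*Protocol article*

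**What the plan says.** All of this is in the protocol article, Sample size calculation, subsection Statistical analysis.

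- Method: "The two-sample *t* test for noninferiority statistical analysis was used for the sample size calculation".
- Null hypothesis: that "the refractive error, measured by SER, will be worse with DIMS lenses than with PALs". Its rejection is said to be "powered to detect a noninferiority margin (Δ) of < 10" per cent. No base for the percentage and no value in diopters is given.
- Effect inputs: "the 2-year difference in myopia progression with DIMS is 0.44 ± 0.09, whereas the difference in myopia progression with PALs is 0.20 ± 0.08".
- Difference carried forward: "Thus, the mean difference between DIMS lenses and PALs is 0.22".
- Spread: "Because the detected variation in myopia is ~ 0.25–0.5, we chose 0.5 as the SD factor".
- Error rates: significance level 0.05, two-sided 95% interval, 80% power, 1:1 allocation.
- Result: "Based on these parameters, the estimated sample size for each group is 201 subjects".

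The same subsection expects about 40% loss over 3 years and arrives at 282 per group. The next subsection, IMI recommendation, settles on 300 per group after also considering published group sizes. Noninferiority of DIMS to PALs is stated as the aim under Aim of the study and again under Primary outcome.

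**The concern.** Two things do not fit. First, the paragraph's inputs and its stated difference disagree by 0.02. Second, an expected DIMS advantage works in favour of a noninferiority claim. The distance to be detected is the advantage plus the margin, so a clear advantage should lead to a small sample. A figure of 201 is several times larger than that, yet about half of what equal lenses would need at a 0.10 D margin.

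At stake is the power claim for the primary endpoint. If 201 answers a different question, the 80% says nothing about the test the trial will report. A reader could not then tell which hypothesis was planned, or how to weigh a failure to show noninferiority.

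**Working it through.** **Inputs.** SD 0.5, two-sided 0.05 (z = 1.960), 80% power (z = 0.842) and effects 0.44 and 0.20, all from the Statistical analysis subsection; 300 per group from IMI recommendation. The margin in diopters is not stated. I assume a range: 0.10 D (10% read as 0.10), 0.044 D (10% of 0.44), 0.022 D (10% of 0.22) and 0.02 D (10% of 0.20).

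**Step 1, the subtraction.** 0.44 − 0.20 = 0.24, not 0.22.

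**Step 2, the formula.** Per group, n = 2 × SD² × (1.960 + 0.842)² / d² = 3.924 / d², rounded up. Here d is the distance between the expected true difference and the null boundary.

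**Step 3, what 201 implies.** d = √(3.924 / 201) = 0.1397 D.

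**Step 4, routes that reproduce 201.**
- 0.24 − 0.10 = 0.14 D: 3.924 / 0.0196 = 200.2, so 201 per group. This uses the correct subtraction rather than the printed 0.22, and reads 10% as 0.10 D.
- 0.22 − 0.022 = 0.198 D, with the formula for total N: 4 × 0.25 × 7.849 / 0.0392 = 200.2, so 201. This uses the printed 0.22 and a relative 10%, but the result would be a total, reported as per group.

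Both subtract the margin from the expected advantage. That places the null boundary at DIMS better by the margin, which is superiority by a margin.

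**Step 5, what the declared test needs.** For noninferiority the null boundary is DIMS worse by the margin.

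| Assumed truth | Margin (D) | d (D) | n per group |
|---|---|---|---|
| DIMS better by 0.24 | 0.10 | 0.34 | 34 |
| DIMS better by 0.22 | 0.10 | 0.32 | 39 |
| DIMS better by 0.24 | 0.02 | 0.26 | 59 |
| DIMS better by 0.22 | 0.02 | 0.24 | 69 |
| Equal | 0.10 | 0.10 | 393 |
| Equal | 0.044 | 0.044 | 2,028 |
| Equal | 0.022 | 0.022 | 8,109 |

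Other readings of the printed 0.22 also miss 201. Plain superiority at 0.22 needs 82. Taking 0.10 off 0.22 gives 273, or 215 at one-sided 0.05.

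**Step 6, power of the planned trial.** Evaluable per group: 300 × (1 − 0.40) = 180. Standard error: 0.5 × √(2 / 180) = 0.0527 D. Power = Φ(d / 0.0527 − 1.960).

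- DIMS better by 0.22, margin 0.02 (d = 0.24, the least favourable of the advantage cases): Φ(2.59) = 99.5%.
- DIMS better by 0.24, margin 0.10 (d = 0.34): above 99.9%.
- Equal, margin 0.10: Φ(−0.06) = 47.5%.
- Equal, margin 0.044: Φ(−1.13) = 13%.
- Equal, margin 0.022: Φ(−1.54) = 6%.

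**The case against.** The best defence is that nothing here shows the trial to be too small. The 300 per group rests partly on published group sizes (125 to 333 for spectacle trials), and on the plan's own expected difference the noninferiority test has more than 99% power. The figure of about 47% arises only at equality, which the paragraph does not assume. All of this stands. It limits the consequence, but it does not make 201 the answer to the stated question.

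Some stronger readings go beyond the documents:

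- *That 201 was certainly built as 0.24 − 0.10.* A second route using the printed 0.22 reaches 201 equally well, and the t-test version of the 0.14 D calculation gives 202. The documents do not show which route was taken.
- *That 0.22 is the misprint and should become 0.24.* Any of 0.44, 0.20 and 0.22 could be wrong. The article alone cannot settle it.
- *That DIMS is expected to be worse, because 0.44 is more progression than 0.20.* The wording permits this, and noninferiority at these margins would then be false. But Background sets the defocus evidence against single-vision lenses, and Rationale for the study design says only lenses already found effective are tested. Benefit is the likelier meaning. What remains is that the direction is not stated.
- *That an SD of 0.5 is too small.* The plan takes the upper end of its own stated range, and the article gives no larger value to test against.

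**Conclusion.** The point holds. The printed difference disagrees with its two inputs. No noninferiority calculation on the stated SD, alpha and power gives 201 per group at the expected advantage, where 34 to 69 suffice, or at equality with a 0.10 D margin, where 393 are needed. The routes found that reproduce 201 size superiority by a margin. The 80% is therefore not the power of the declared primary test.

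This rests on reading 0.44 and 0.20 as benefits with DIMS the better lens, and on a margin between 0.02 and 0.10 D, since the document states none in diopters. The power at equality depends heavily on that margin: about 47% at 0.10 D, 13% at 0.044 D and 6% at 0.022 D. A reader might infer that the trial is underpowered. That does not follow under the planning assumption. It would be true at equality for each of these margins.

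**What to change.** Rewrite the sample size paragraph:

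1. Reconcile 0.44, 0.20 and 0.22 against their sources.
2. Say whether the inputs are benefits, against which comparator, and which lens is expected to be better.
3. State the noninferiority margin in diopters.
4. Recompute the size with d equal to margin plus expected advantage.
5. Replace the 80% with the power that 300 randomised (180 evaluable) per group gives, both at the expected advantage and at equality.

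A superiority test after noninferiority has been shown is optional. It is not needed to repair this point.

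The cost is one paragraph, with 300 per group unchanged. The downside is a conditional and less favourable power statement: above 99% if DIMS is as much better as expected, but under 50% at equality for each margin considered here.

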#### IMI recommendation

The IMI summarized key issues in view of more than 170 peer-reviewed published articles on myopia control, and more than 85 multidisciplinary experts contributed to reports on clinical practice, basic research, and future directions [6–8, 15]. According to these IMI reports, key information about the sample size calculation is missing in published articles, and a reasonable number of subjects per group ranges from ~ 70 to 333 children over 2 to 3 years of follow-up [15]. In particular, the sample size per group for spectacles ranges from 125 to 333 [15].

Based on the expert consensus of the reviewed articles and the statistical calculation, a sample of 300 eligible children will be required in each arm of the trial. We do not plan to stratify any subgroups.

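### The 40% loss allowance is applied as 201 × 1.4 = 282 instead of 201 / 0.6 = 335, so the adopted 300 per arm leaves 180 evaluable, below the plan's own 201

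*Protocol article*

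**What the plan says.** All of this stands in the protocol article under Sample size calculation.

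- **Statistical analysis** subsection. The calculation uses a two-sample *t* test for noninferiority with "a significance level of 0.05, 95% confidence interval (two-sided), 80% power, and 1:1 allocation". For the spread, "we chose 0.5 as the SD factor". The result is: "Based on these parameters, the estimated sample size for each group is 201 subjects". On attrition, "we estimated the rate of subject loss to follow-up over 3 years to be ~ 40" per cent. The section ends: "Considering these factors together, the estimated sample size for each group is 282".
- **IMI recommendation** subsection. From the expert consensus and the calculation together, it concludes that "a sample of 300 eligible children will be required in each arm of the trial". It cites a range of 125 to 333 per group for spectacle trials.

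Two other places bear on who is evaluable. Primary outcome defines progression over 3 years as the change in subjective SER from baseline to the last follow-up visit. Data management and data analyses includes all randomized participants, plans repeated measures analysis of variance, and rules out imputation after dropout.

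**The concern.** A loss allowance exists so that the number left after dropout equals the number the power calculation requires. Multiplying by (1 + loss) does not achieve this, because the 40% is lost from the larger enrolled number and not from 201. The two methods nearly agree when loss is small but differ widely at 40%.

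The adopted 300 is larger than 282, so it looks like a small reserve. Against the correctly inflated figure it is a deficit. At stake is whether the trial, at the attrition it expects, has the evaluable number that its stated power is built on.

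**Working it through.** **Inputs**, all from the Statistical analysis and IMI recommendation subsections: 201 per group before loss; loss about 40%; 282 per group after the allowance; 300 per arm adopted; two-sided 0.05; 80% power; SD 0.5.

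**Step 1: reproduce 282.**
n × (1 + loss) = 201 × 1.40 = 281.4, rounded up to 282. This matches the protocol exactly.

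**Step 2: the inflation that retains 201.**
n / (1 − loss) = 201 / 0.60 = 335 per group, or 670 in total against the planned 600. Check: 335 × 0.60 = 201.

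**Step 3: what the stated sizes leave at 40% loss.**

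| Enrolled per arm | Evaluable at 40% loss | Shortfall from 201 | Largest loss that keeps 201 |
|---|---|---|---|
| 282 | 282 × 0.60 = 169 | 32 | 1 − 201/282 = 28.7% |
| 300 | 300 × 0.60 = 180 | 21 | 1 − 201/300 = 33.0% |
| 335 | 335 × 0.60 = 201 | 0 | 40% |

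**Step 4: power, assuming only that 201 gives 80%.**
For a comparison of two means, the expected test statistic grows with √n. Power at n is therefore Φ[(1.96 + 0.8416) × √(n/201) − 1.96] at two-sided 0.05.

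- n = 180: √(180/201) = 0.9463; 2.8016 × 0.9463 − 1.96 = 0.691; power 75.5%.
- n = 169: √(169/201) = 0.9170; 2.8016 × 0.9170 − 1.96 = 0.609; power 72.9%.

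With a one-sided 0.05 level the same scaling gives 76.1% and 73.7%. So power is about 76% at 180 and about 73% at 169. This step needs no margin or effect size.

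**Step 5: can 201 itself be reproduced?**
The protocol states a mean difference of 0.22 and is "powered to detect a noninferiority margin (Δ) of < 10" per cent, with no unit. Of the combinations tried, only one returned 201: a distance of 0.24 − 0.10 = 0.14 with SD 0.5, which gives 2 × (1.96 + 0.8416)² × 0.5² / 0.14² = 200.2, rounded up to 201 (202 with the noncentral *t*). On that reconstruction, power is 75.7% at 180 and 73.0% at 169 by the normal approximation (75.5% and 72.8% by the *t* distribution), in line with step 4. The value 0.14 is inferred. The protocol does not state it, and it relies on 0.44 − 0.20 = 0.24 where the text gives 0.22.

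Other readings of the inputs give very different power at 180 per arm:

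- margin 0.10 with no true difference: 47.5%;
- 0.22 − 0.10 = 0.12: 62%;
- 0.22 + 0.10 = 0.32: over 99%.

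**The case against.** **The base figure is doubtful, so a power cannot be quoted.** This stands in part. A reader might infer that the trial simply has 75.5% power and not 80%. The documents do not support that as an unconditional statement: it holds only if 201 gives 80%, and step 5 shows how far power moves under other readings. The error in the loss step does not depend on this, because dividing by 0.60 is right whatever base is used.

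**300 is not 282 rounded up.** This is correct. The protocol gives two sources for it, the calculation and the consensus range of 125 to 333. But as the protocol reports it, that range carries neither a power nor a loss rate, so it cannot supply the missing allowance.

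**Children lost late may still contribute.** Repeated measures analysis of all randomized participants, with change taken to the last visit, might use some of their data. That could soften the loss of information. It does not rescue the calculation, which is for a two-sample *t* test of 3-year change and itself treats lost children as needing replacement.

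**The 40% is approximate.** It is, but 300 retains 201 only at 33% loss or less, and 282 only at 28.7% or less. Neither is close to 40%.

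**Covariate adjustment would close the gap.** A reader might infer that adjusting for baseline SER and age makes up the difference. Full recovery would need those covariates to explain about 1 − 180/201 = 10% of the outcome variance. The protocol gives no correlation or explained variance, so this cannot be claimed.

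**Conclusion.** The inflation is wrong as written. The figure of 282 should be 335, and at the plan's own expected loss the adopted 300 per arm leaves 180 evaluable against a stated need of 201. Nothing else in the article repairs this.

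The effect is modest: about 76% power at 180 per arm, a drop of 4 to 5 percentage points, on the assumptions that 201 gives 80%, that loss is 40% in each arm, and that lost children contribute nothing to the 3-year comparison. It would be too strong to say that the trial is shown to be underpowered in absolute terms, since the validity of 201 is a separate question. This is a should-fix correction of the sample size justification. It does not by itself call for a change of design or analysis.

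**What to change.** 1. In the Statistical analysis subsection, replace 282 with 335 and show the formula, 201 / (1 − 0.40).
2. In the IMI recommendation subsection, stop describing 300 as the number required. Suggested wording: *We will enrol 300 children per arm. At 40% loss over 3 years this leaves about 180 evaluable per arm, with about 76% power if 201 evaluable per arm gives 80%. The 201 are retained only if 3-year loss is 33% or less.*
3. If the base figure is revised when the 0.22 versus 0.24 discrepancy and the unit of the margin are settled, redo the loss step by division and update the figures above.

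The cost is a few sentences and a less favourable stated power. Keeping 300 per arm needs no extra children. Enrolling the full 335 would add 35 per arm, 70 in total.
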